### Intervention description {11a}

The description of the intervention below has been reported in accordance with the TIDieR (Template for Intervention Description and Replication) guidelines [32].

DTs will visit care homes in their locality every 6 months, and the DNs will visit every month for the first 3 months and then 3-monthly afterwards. This approach builds on the existing Gwên am Byth programme (which has not been empirically evaluated) [29]. In this manner, DTs will proactively oversee the clinical management of eligible dentate residents. The DTs will provide any simple operative treatment for individual residents, within their Scope of Practice (referring onto dentists within the CDS when necessary) [33]. Monaghan and Morgan [26] found that these management strategies would address the majority of cases that are likely to be seen in residents based in care homes. Extractions will need to be referred to dentists and DTs will act to sign-post residents to the CDS. Other clinical cases which may require onwards referral are fractured dentures, crowns and bridges, but these are less likely to warrant further intervention, given the focus on palliative management in this context [34].

The DNs will promulgate advice to improve the day-to-day prevention offered to residents based on Delivering Better Oral Health [35]. This will include the following:Professional application of prescribed fluoride (2.2% NaF varnish) every 3 months5000 ppm fluoride toothpaste, prescribed as appropriateOral hygiene advice; andRecommendation of the Eatwell Guide [36].

The visits from the DNs will form an important function in terms of championing oral health amongst care home managers and staff. This element of the complex intervention is just as important as the 6-monthly clinical management of dental need by the DTs. As highlighted by Brocklehurst et al. [37], ‘there is growing support for the use of change agents in implementation processes’. Human agency where clinical or non-clinical staff act as change agents to facilitate the enactment of complex interventions is increasingly seen to be key [38–40]. To facilitate this process, training materials will be provided using the All-Wales Faculty of Dental Care Professionals platform [41]. This will include dedicated documents for care home staff, based on a funded study that has utilised co-production and co-design principles to adapt NICE guidelines NG48 (TOPIC) [28]. Hard-copy training manuals will also be provided to care homes.

The local study team will be responsible for reviewing the delivery of the intervention so that it meets the criteria of the trial, i.e. a visit by the DT at least once every 6 months and by the DN once a month in the first quarter and then 3-monthly afterwards.

### Criteria for discontinuing or modifying allocated interventions {11b}

Care homes and residents will be able to withdraw at any time during the study. Where possible, in agreement with participants, data from those withdrawn will be used in analysis unless consent for this is specifically withdrawn.

### Strategies to improve adherence to interventions {11c}

There will be no additional strategies to improve the adherence to the intervention. Adherence to the intervention will be monitored by collecting information on completion rates (fully, partially or not completed) for the following: (1) weekly oral symptoms checklist collected by care home staff and (2) completed care home staff training.

### Relevant concomitant care permitted or prohibited during the trial {11d}

The intervention will be delivered alongside any oral care practices currently in place in the care homes. Care homes will not be asked to cease any practices that they are currently undertaking in either the control or intervention arm.

### Provisions for post-trial care {30}

Cover for harm as a result of the design or conduct of the trial has been arranged with the study Sponsor (Bangor University). In the event of complaints and concerns, these can be directed towards the research team, and participants will have the relevant contact details. Clinical treatment provided by the DTs and DNs will be covered by their individual or organisation’s indemnity. Care homes in the intervention arm can retain the hard-copy training manuals. The training manuals will also be made available to the control arm care homes after the end of the study.

### Outcomes {12}

#### Primary outcome in the trial

The Primary Outcome Measure (POM) for this study will be the Silness-Loë Plaque Index [42]. The index is a 4-point scale (measuring the amount of dental plaque present on six index teeth) ranging from 0-no plaque to 3-abundance of dental plaque within the gingival pocket and/or on the tooth and gingival margin. In accordance with the index, the mean will be calculated from these ordinal scores on the six index teeth. The prevailing model in the dental literature is to measure the change in this mean score. However, this model is difficult to infer clinical significance at a population level. To this end, the proportion of individuals in each arm that have demonstrated a 50% reduction in their mean Silness-Loë Plaque Index from baseline will be calculated. This will enable the change in the mean plaque index at the individual level to be measured, whilst providing a meaningful primary outcome measure at a population level.

The sample size calculation (see section ‘Sample size {14}’) is based and powered on changes to the POM at 6 months. This takes account of the ‘time-to-effect’ of the intervention on the POM and the pragmatic consideration of the length of stay of eligible residents. However, a follow-up at 12 months will be undertaken to determine whether the effect seen at 6 months can be sustained. This aligns with the eligibility criteria and the estimated length of stay that the residents have in a care home [43].

#### Secondary outcomes

Clinical outcomes (assessed at baseline, 6 months and 12 months) will include the number of new carious lesions (coronal and root caries) and episodes of bleeding on probing. This will be undertaken on the same index teeth (according to Ramfjord) to reduce the burden on participating residents [44];Health−related quality of life (HRQoL) will be assessed at baseline, 6 months and 12 months using the EuroQol five dimensions questionnaire (EQ−5D5L) [45]. The EQ−5D5L is an established HRQoL outcome and is also relevant for a cost−utility analysis;Oral health−related quality of life (OHRQoL) will be assessed at baseline, 6 months and 12 months using the Oral Impacts on Daily Performances (OIDP) [46]. This will assess the impacts of oral conditions on daily life. It is a widely used OHRQoL outcome also applied in care homes in the UK;Oral symptoms, episodes of pain and episodes of unscheduled care; andThe number of onward referrals to dentists, when the treatment needed extends beyond the DTs’ Scope of Practice [33].

#### Cost-effectiveness analysis

A parallel cost-effectiveness analysis from an NHS perspective will be undertaken and will examine potential long-term costs and benefits of the intervention. A cost-effectiveness model will be produced.

### Participant timeline {13}

Figure 2 provides an overview of the study timeline. Care homes will be informed about the study and screened for eligibility (*t*_−2_). Eligible care homes who are interested in taking part will be recruited, then randomly allocated to the intervention or control arm (*t*_−2_). Residents within the recruited care homes will be initially screened by the care home manager. The local study team will then confirm eligibility, and from the residents that have been chosen, select a random sample of eligible residents for the trial (*t*_−1_). Eligible residents or their Personal Consultee will then be asked to provide informed written consent (*t*_−1_).

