### Recruitment {15}

Recruitment will be a two-stage process. The first stage will be the recruitment of the care homes. The study will be conducted in 40 care homes (with expected 50% recruitment rate, 80 homes will be approached). Eligible care homes will be informed about the study through the standard communication routes (letter/email/phone call or in person) and in collaboration with Care Forum Wales [50], ENRICH-Cymru [51] and ENRICH in London [52]. The research team will also use the footprint of participating CDSs across Wales, Northern Ireland, Central and North London and the North of England. If eligible care homes want further information, a member of the local study team will arrange a visit in person to provide the care home managers with an information sheet, further discuss the study and answer any questions about participation. At least 48 h after discussing the study, eligible care homes will be contacted by the researcher to confirm whether they would like to take part or not.

The second stage will be the recruitment of eligible residents in participating care homes. The aim is to recruit approximately seven residents per home resulting in an estimated sample size of 280 residents. The care home managers will be responsible for initially screening the residents to determine who meets the eligibility criteria. All staff involved in the recruitment of participants will be trained on the eligibility criteria prior to site activation. A short presentation about the study will be provided to potentially eligible residents and/or their Personal Consultees. Those interested in participating will be given a PIS and an ICF. The local study team will attend the care home at least 48 h after discussing the study so that potential participants can ask questions about the study and express their interest in taking part. Before any trial-specific procedures are performed, the participant will need to sign and date the ICF.

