### Concealment mechanism {16b}

Local study team members will allocate the care homes using a dynamic adaptive randomisation algorithm [53].

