### Implementation {16c}

Since this is a cluster RCT, residents will be allocated to the treatment that have been assigned to the care home. An independent NWORTH member of staff will allocate the care homes and a member of the local study team will enrol residents on to the study.

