## Assignment of interventions: blinding

### Who will be blinded {17a}

It is not possible to blind the care homes, the individual residents in the trial or outcome assessors, but the trial statistician will remain blind throughout the duration of the study, until the blinded analysis detailed in the statistical analysis plan has been conducted and reported to the study team.

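### Homes are randomised before their residents are screened, chosen, consented and examined, which leaves the primary comparison open to recruitment bias

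*Protocol article*

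**What the plan says.** The Participant timeline {13} fixes the order of events:

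- **t-2, homes:** "Eligible care homes who are interested in taking part will be recruited, then randomly allocated to the intervention or control arm".
- **After allocation, first selection:** "Residents within the recruited care homes will be initially screened by the care home manager". Recruitment {15} repeats this: "The care home managers will be responsible for initially screening the residents to determine who meets the eligibility criteria".
- **t-1, sampling:** "The local study team will then confirm eligibility, and from the residents that have been chosen, select a random sample of eligible residents for the" [...].
- **t-1, consent:** "Eligible residents or their Personal Consultee will then be asked to provide informed written consent". The consent section {26a} gives this task to the local study team.
- **t0, baseline:** the first dental examination follows these steps.

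On blinding, section {17a} says: "It is not possible to blind the care homes, the individual residents in the trial or outcome assessors". Only the trial statistician is kept blind.

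Two adjacent sections disagree on who allocates. Concealment mechanism {16b} says: "Local study team members will allocate the care homes using a dynamic adaptive randomisation algorithm". Implementation {16c} says: "An independent NWORTH member of staff will allocate the care homes and a member of the local study team will enrol residents".

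Under Outcomes {12}, a success is a resident whose mean plaque index falls by 50% from baseline.

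**The concern.** Cluster randomisation makes the homes comparable. It makes the residents comparable only if they are identified, and agree to join, independently of the arm. Here the steps that determine who enters come after allocation, and nothing hides the arm from the people who carry them out.

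The incentives also differ by arm. Intervention residents are offered therapist visits, simple treatment and fluoride varnish. Control residents continue with usual care, and their homes receive the training manuals only after the study. The internal pilot counts recruitment of 50% of eligible residents as green, so there is ample room for different residents to join in each arm.

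The arms could then differ in cooperation, cognition, dentition or baseline plaque, all of which plausibly affect who halves the index. The baseline score is also the denominator of the outcome. If an unblinded examiner scores it higher in intervention homes, halving becomes easier there with no treatment effect. Intention to treat keeps the recruited groups intact, but it cannot restore comparability lost at recruitment. The covariates named for the primary model are site and home size.

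**Working it through.** **1. Knowledge of allocation at each step, as written**

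| Step | Who | Protected from knowing the arm? |
|---|---|---|
| Initial screening | Home manager | No: homes are unblinded {17a} |
| Eligibility check, sampling | Local study team | No: {16b} has the team allocate; under {16c} nothing keeps it blind, and it also reviews intervention delivery {11a} |
| Consent | Resident or consultee, with local study team | No: residents are unblinded {17a} |
| Baseline plaque score | Community Dental Service examiner | No: assessors are unblinded {17a}, though separate from delivery {18a} |

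The random draw is taken from residents already put forward and comes before consent. It limits choice by the study team but undoes neither the manager's selection nor differential consent.

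**2. The plan's own power figure**

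Inputs from Sample size {14}: 20 homes per arm, 5 completers per home, ICC 0.05, proportions 0.10 and 0.29, 5% significance (sidedness not stated; two-sided assumed).

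- Completers per arm: 20 × 5 = 100.
- Design effect: 1 + (5 − 1) × 0.05 = 1.20.
- Effective n per arm: 100 / 1.20 = 83.3.
- Unpooled standard error: √[(0.10 × 0.90 + 0.29 × 0.71) / 83.3] = 0.0596.
- Power: Φ(0.19 / 0.0596 − 1.96) = 0.89. With the pooled variance under the null it is 0.88.

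The stated 90% is therefore approximately reproduced, and 83.3 is a fair basis for the illustration.

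**3. Effect of a shift caused by recruitment alone**

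Assume no true effect and a control proportion of 0.10, and let selection raise the intervention proportion to 0.10 + b. The chance of a significant result favouring the intervention is Φ[(b − 1.96 × SE0) / SE1], where SE0 uses the pooled proportion and SE1 the two separate proportions, each with n = 83.3.

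For b = 0.05:

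- SE0 = √(2 × 0.125 × 0.875 / 83.3) = 0.0512.
- SE1 = √[(0.10 × 0.90 + 0.15 × 0.85) / 83.3] = 0.0511.
- Φ[(0.05 − 0.1004) / 0.0511] = Φ(−0.99) = 0.16.

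| Assumed shift b | Chance of a false positive favouring the intervention |
|---|---|
| 0 (nominal) | 2.5% |
| 0.02 | 6% |
| 0.05 | 16% |
| 0.08 | 32% |
| 0.10 | 44% |

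**4. How small a baseline error produces such shifts**

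Assume the log of the 6-month to baseline ratio is normal with SD s, centred so that 10% of residents halve their score. If baseline alone is over-scored by a fraction k, the proportion becomes Φ[ln(1 + k) / s − 1.28]. For s from 0.6 down to 0.4:

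- k = 5%: 0.115 to 0.123.
- k = 10%: 0.131 to 0.148.
- k = 20%: 0.164 to 0.204.

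Under these assumptions, over-scoring baseline by 5% to 10% in one arm produces shifts of roughly 0.02 to 0.05.

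**The case against.** The best defence is that the protocol limits discretion and would make imbalance visible. The resident criteria are largely objective: age, at least six natural teeth, full-time residence, not solely end-of-life or palliative care. Recruiting staff are trained on eligibility. A log is kept of residents who decline or cannot consent. Cognitive scores are recorded and their effect on the primary outcome is examined. Examiners are kept apart from delivery. These measures narrow or reveal the problem, but none conceals allocation at screening, consent or baseline, and judging capacity to consent still leaves room for discretion.

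Some of the objection stands:

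- Section {17a} does not list the local study team among those who cannot be blinded. If {16c} is the correct text, the accurate statement is that the team is not protected from knowing the arm.
- No section says outright that residents are told the allocation before consenting. It is likely, since the home knows and residents are described as unblinded, but it is an inference.
- The size and direction of any shift are assumed. Selection could also work against the intervention.
- The disagreement between {16b} and {16c} is a separate drafting error. Correcting it alone would leave the order of steps unchanged.

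**Conclusion.** The concern holds. As written, allocation precedes every step that determines who enters the trial and the baseline measurement on which the primary outcome depends, and the people carrying out those steps are either stated to be unblinded or not shielded from the allocation. This shows exposure to bias, not that bias will occur.

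The consequence could be material. A spurious shift of 0.05, about a quarter of the 0.19 target difference (0.05 / 0.19 = 26%), would raise the false-positive chance in the intervention's favour from 2.5% to about 16%. These figures rest on the plan's ICC, completers and control proportion, a two-sided 5% test and the assumed shifts. Because the analysis cannot reliably undo selection at entry, this should be corrected before recruitment starts. The Trial status section says recruitment had not begun.

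**What to change.** **Order of steps.** Rewrite the Participant timeline {13} so that in each home these are finished before the home is randomised: screening, a full list of eligible residents, the random draw from that list, consent and the baseline examination. The resident list is then locked, and nobody is added after allocation.

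**Who allocates.** Amend Concealment mechanism {16b} to agree with Implementation {16c}: an independent NWORTH member runs the algorithm once the list is locked. The local study team still recruits residents but takes no part in the allocation.

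This is workable because the dynamic algorithm in Sequence generation {16a} balances on country and bed numbers, both known before any resident is approached.

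**Second best.** If a home must be randomised first, residents should be identified, consented and examined at baseline by people unaware of its allocation. This is weaker, because the manager and residents may still know the arm.

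**Cost.** The protocol and site instructions must be revised. The sample stays at 40 homes and 280 residents, with power still about 89%. The downside is a wait between baseline and delivery. It should be short, because follow-up is timed from baseline, 28% attrition is already planned, and the rule that homes be COVID-free for 14 days may complicate scheduling. The change does not address unblinded assessment at 6 and 12 months.

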**Fig. 2 Fig2:**
[figure not shown]
Time schedule of enrolment, interventions, assessments and visits for participants

The care homes allocated to the intervention arm will be asked to implement the oral health intervention during the study period (12 months, *t*_0_ to *t*_2_), and the care homes allocated to the control arm will be asked to continue with routine practice during the same 12-month period. Assessments (intervention and control group) will be undertaken at baseline (*t*_0_), 6 months after baseline (*t*_1_) and 12 months after baseline (*t*_2_).

### Sample size {14}

The primary outcome will be based on a binary outcome using a superiority design, with a successful case demonstrating a 50% reduction in their mean Silness-Löe Plaque Index [42] over a 6-month period, i.e. the relative proportion of the residents whose Silness-Löe Plaque Index have been halved as a result of the intervention will be compared across the two arms. This concurs with two relevant studies, which tested the implementation of an oral hygiene guideline in a comparable population. Khanagar et al. [47] demonstrated a 50% reduction in the mean Silness-Löe Plaque Index (3.17 to 1.57), and the mean reduction amongst residents found by van der Putten et al. [48] was from 2.36 to 1.58. Assuming the proportion of the control group that will halve their mean Silness-Löe Plaque Index over 6 months is 0.10 (given the halo effect of participating in a trial), a sample of 280 (20 care homes per arm with five completers per care home plus attrition at 28%) will provide 90% power to detect a 0.19 difference in proportions between the arms at a 5% significance level (i.e. 0.29 of intervention group will see a 50% reduction in their mean Silness-Löe Plaque Index). This incorporates an intraclass correlation coefficient of 0.05. The measurements taken at 12 months will determine whether this effect (the primary end point being 6 months) can be sustained for a further 6 months.

It is likely that care homes will be able to recruit a variable number of participants due to their relative size and differing populations. Therefore, a coefficient of variation has been included in the sample size to accommodate this. Taking the approach of Campbell and Walters [49] and assuming that recruitment will vary between 5 and 15 participants within a home the sample proposed will accommodate this and still retain 90% power.

### Recruitment {15}

Recruitment will be a two-stage process. The first stage will be the recruitment of the care homes. The study will be conducted in 40 care homes (with expected 50% recruitment rate, 80 homes will be approached). Eligible care homes will be informed about the study through the standard communication routes (letter/email/phone call or in person) and in collaboration with Care Forum Wales [50], ENRICH-Cymru [51] and ENRICH in London [52]. The research team will also use the footprint of participating CDSs across Wales, Northern Ireland, Central and North London and the North of England. If eligible care homes want further information, a member of the local study team will arrange a visit in person to provide the care home managers with an information sheet, further discuss the study and answer any questions about participation. At least 48 h after discussing the study, eligible care homes will be contacted by the researcher to confirm whether they would like to take part or not.

The second stage will be the recruitment of eligible residents in participating care homes. The aim is to recruit approximately seven residents per home resulting in an estimated sample size of 280 residents. The care home managers will be responsible for initially screening the residents to determine who meets the eligibility criteria. All staff involved in the recruitment of participants will be trained on the eligibility criteria prior to site activation. A short presentation about the study will be provided to potentially eligible residents and/or their Personal Consultees. Those interested in participating will be given a PIS and an ICF. The local study team will attend the care home at least 48 h after discussing the study so that potential participants can ask questions about the study and express their interest in taking part. Before any trial-specific procedures are performed, the participant will need to sign and date the ICF.

